## Abstract

**Background:**

Neuropathic pain (NP) (including painful diabetic neuropathy, postherpetic neuralgia, etc) affects approximately 7% to 8% of the population and is associated with a devastating symptom burden as well as a profound economic impact for patients, their families, and the health care system. Current therapies have limited efficacy and dose-limiting adverse effects (AEs). Rational combination therapy with carefully selected NP drugs has shown potential for measurable improvements in pain relief, quality of life, and health care use. Today, over half of NP patients concurrently receive 2 or more analgesics but combination use is based on little evidence. Research is urgently needed to identify safer, more effective combinations.

**Objective:**

We hypothesize that analgesic combinations containing at least 1 nonsedating agent would be as safe but more effective than either monotherapy without increasing overall AEs because of additive pain relief. Pregabalin (PGB), a sedating anticonvulsant, is proven effective for NP; the antioxidant alpha-lipoic acid (ALA) is one of the only nonsedating systemic agents proven effective for NP. Thus, we will conduct a clinical trial to compare a PGB+ALA combination to each monotherapy for NP.

**Methods:**

Using a double-blind, double-dummy, crossover design, 54 adults with NP will be randomly allocated to 1 of 6 sequences of treatment with PGB, ALA and PGB+ALA combination. During each of 3 different treatment periods, participants will take 2 sets of capsules containing (1) ALA or placebo and (2) PGB or placebo for 31 days, followed by an 11-day taper/washout period. The primary outcome will be mean daily pain intensity (0-10) at maximally tolerated dose (MTD) during each period. Secondary outcomes, assessed at MTD, will include global improvement, adverse events, mood, and quality of life.

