### Sample Size

Based on previous estimates of within-patient variation, variance=2.3, from our previous study in NP [15], we calculate that a sample of 55 trial completers would provide an 80% chance of detecting (alpha=0.05) a mean treatment difference of 1 point (0-10 scale). For a sample size divisible by 6, the number of treatment sequences, we adjusted the sample size to 54 trial completers.

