## Discussion

NP remains a challenging condition to treat, with current analgesic drugs providing only partial relief, often at the risk of disabling AEs. To the best of our knowledge, this proposed trial is the first to compare the combination of an anticonvulsant with an antioxidant to treat NP. Because ALA and PGB have different AE profiles, we expect their combination to provide superior analgesic efficacy in NP without increasing AEs.

Potential threats to completing this trial include challenges with participant enrollment, noncompliance, protocol violations, and early dropouts. However, we are confident that the proposed trial design and our experience with recent and previous RCTs will minimize these concerns. Also, noncompliance, protocol violations, and early dropouts will be minimized by the crossover design as well as thorough patient teaching and careful follow-up of trial patients.

As discussed above, there is an urgent need for improved NP treatments with better analgesic efficacy and better safety and tolerability. Thus, this trial shall provide rigorous evidence for a potentially improved treatment strategy for NP.

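### The number 54 is given both as patients randomised and as completers, with no allowance for the dropout that the protocol itself anticipates

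*Protocol article*

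**What the plan says.** The abstract (Methods) of the protocol article states that "54 adults with NP will be randomly allocated to 1 of 6 sequences of treatment".

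The Sample Size section counts completers. It starts from a variance ("Based on previous estimates of within-patient variation, variance=2.3"), arrives at "a sample of 55 trial completers would provide an 80% chance of detecting (alpha=0.05) a mean treatment difference of 1 point (0-10 scale"), and then, to obtain a multiple of the six sequences, says "we adjusted the sample size to 54 trial completers". It gives no dropout rate and no number to randomise. Trial Design and Participant Allocation give no number to randomise either.

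Other sections provide for patients who do not complete:

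- The Discussion says: "Potential threats to completing this trial include challenges with participant enrollment, noncompliance, protocol violations, and early dropouts".
- Trial Design requires discontinuation when a pain exacerbation leads the patient to want a new therapy, and keeps such patients in the analyses.
- Trial Duration and Follow-Up Frequency plans telephone follow-up of patients withdrawn early.
- Statistical Analyses plans for patients with data from only one period, and adds a pattern-mixture sensitivity analysis for missing data.

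**The concern.** Randomised patients and completers are the same 54 people only with zero attrition. The trial runs for 18 weeks, with three periods of titration to tolerability, and the article plans for early withdrawal in several places.

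The enrolment target is therefore undefined. If recruitment stops at 54 randomised, fewer than 54 will probably complete, and the Sample Size section describes a trial that will not be run. If recruitment continues until 54 complete, more than 54 will be randomised and the abstract is wrong. The two readings differ in the number of patients exposed, in when recruitment ends, and in the power that can be claimed.

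**Working it through.** **Inputs.** From Sample Size: within-patient variance 2.3, difference 1 point, alpha 0.05 (taken as two-sided, since the section does not say), power 80%, 55 completers, then 54 completers. From the abstract: 54 randomised. Dropout is not given, so the rates below are assumptions. Power is for one pairwise contrast, by normal approximation unless stated.

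**1. Does 55 follow from the printed inputs?** A within-patient difference between two treatments has variance 2 × 2.3 = 4.6. Then

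n = 4.6 × (1.960 + 0.842)² / 1² = 4.6 × 7.849 = 36.1,

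so 37, or 38 to 39 with the t distribution. The planned model also has a first-order carryover term. With it, the contrast variance in the six-sequence, three-period design rises from 2 to 2.5 times the within-patient variance, that is 5.75, and n = 5.75 × 7.849 = 45.1, so 46 (47 with t). Neither is 55. Values near 55 appear only with inputs that the section does not state, for example the carryover-adjusted variance with alpha 0.025 (54.7).

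**2. Power if 55 completers = 80% is accepted.** The implied variance of the difference is 55 / 7.849 = 7.01. With n completers, power = Φ(√(n / 7.01) − 1.96).

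**3. Power from the printed inputs.** The same formula, with 4.6 (no carryover term) or 5.75 (carryover term) in place of 7.01.

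| 54 randomised, assumed loss | Completers | Accepting 55 = 80% | Variance 2.3, no carryover term | Variance 2.3, carryover term |
|---|---|---|---|---|
| 0% | 54 | 79.3% | 92.9% | 86.5% |
| 5% | 51.3 | 77.2% | 91.6% | 84.8% |
| 10% | 48.6 | 75.0% | 90.2% | 82.8% |
| 15% | 45.9 | 72.6% | 88.5% | 80.7% |
| 20% | 43.2 | 70.0% | 86.5% | 78.3% |
| 30% | 37.8 | 64.2% | 81.8% | 72.7% |

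These count completers only.

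**4. Where power falls below 80% on the printed inputs.** Without the carryover term, 37 to 39 completers are needed, so the tolerable loss is 1 − 39/54 = 28% to 1 − 37/54 = 31%. With it, 46 to 47 are needed, so 1 − 47/54 = 13% to 1 − 46/54 = 15%.

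**5. If 54 completers is the target.** The number to randomise is 54 / (1 − d): 60 at 10% loss, 68 at 20%, 78 at 30%. Rounded up to a multiple of six, these become 60, 72 and 78.

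**The case against.** The best defence is that only the abstract conflicts. The body of Methods gives no number randomised, and Sample Size speaks of completers throughout. The abstract may simply have shortened the target, with any recruitment allowance left to the full protocol, which is not shown. That is plausible, and the lack of a printed dropout allowance would not be a finding by itself. But here two figures are printed and they disagree, and nothing in the article says which one governs.

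A second defence is that completer counts understate the information. The primary analysis is a linear mixed model with a random patient effect, and a patient with two usable periods adds to a within-patient contrast. This stands: the powers in the table are lower bounds. The step from 55 to 54 is also explained in the text and costs only 0.7 of a percentage point (80.0% to 79.3%).

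A reader might go further and infer that any dropout at all takes the trial below its stated power. The document does not support that. It follows only if 55 completers = 80% is taken as correct, and the section's own variance, difference and alpha do not give 55. On those inputs there is room for a substantial loss.

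A reader might also point to the power to show superiority over both monotherapies at once, which with the carryover term is about 77% to 78% at 54 completers and lower with dropout. Sample Size makes no such claim. It states power for a single mean difference, and at 54 completers that shortfall comes from changing the target rather than from dropout.

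**Conclusion.** The contradiction stands: 54 cannot be both the number randomised and the number of completers unless nobody leaves the trial, and the article expects some to leave.

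The effect on power depends on a figure that the article does not explain. Taking 55 completers = 80% at face value, 54 randomised falls short: about 75% at 10% loss and 70% at 20%. From the printed variance of 2.3, per-contrast power is about 93% at 54 (87% with the carryover term) and stays at or above 80% until roughly 28% loss (13% to 15% with that term). These results assume a two-sided 0.05 test of one contrast, completers only, and dropout rates that are ours. It is therefore not established that the trial is underpowered. What is established is that the enrolment target is ambiguous and that the stated power cannot be attached to it.

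**What to change.** Make the abstract and the Sample Size section state the same quantity.

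- If 54 is the number randomised, say so in Sample Size, state the dropout assumed, and restate power at the number of completers expected.
- If 54 completers is the target, say in the abstract that randomisation continues until 54 have completed, give the expected number randomised, and say that all randomised patients are analysed.

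In either case, show the inputs behind 55: sidedness, alpha per comparison, the variance of the contrast, and whether the carryover term is included. The restated power will then be correct.

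The first option costs wording and a recalculated power figure, with no extra patients. The second makes explicit a recruitment commitment above 54: 60 patients at 10% loss, and 68 at 20% (72 if kept to a multiple of six).

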### Aims and Hypothesis

The objective of this trial is to compare the safety and efficacy of a PGB+ALA combination to each monotherapy in treating participants with NP. Our primary hypothesis is that PGB+ALA has greater analgesic efficacy versus either monotherapy.

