### Trial Design

We have designed a single center double-blind, double-dummy, randomized, controlled, 3-period crossover trial (compliant with Health Canada; International Conference on Harmonization; Methods, Measurement, and Pain Assessment in Clinical Trials; and Consolidated Standards of Reporting Trials [CONSORT]) comparing a PGB+ALA combination to monotherapy in treating NP (Figures 1 and 2). Using a flexible dose titration, Latin Square crossover design, treatments will be titrated during each of 3 treatment periods to maximal tolerated dose (MTD) with primary and secondary trial analyses comparing the 3 treatments using end-of-period outcomes. Given ethical issues and since PGB and ALA are proven with multiple trials confirming superiority over placebo [19,20], this active control superiority design does not include a placebo alone treatment. Furthermore, our previous trials [14-16] have confirmed assay sensitivity with a similar design. Internal validity of our crossover design is supported by stability of NP over time [14-17,31] and the risk of carryover from one period to the next is very low because each period is followed by an 11-day dose taper and drug washout, and the final MTD week for each period (from which the primary outcome is obtained) is separated from the next period’s final week by 7 weeks (ie, ≥20 half-lives of the drugs studied). Nevertheless, exploratory analyses will be conducted to identify if any low-order carryover effect does exist.

During each of 3 trial periods, using a double-blind randomized crossover design, patients will receive 2 sets of capsules (Figure 3): (1) blue capsules (ALA 300 mg or placebo) and (2) gray capsules (PGB 75 mg or placebo). During the combination period, blue will contain ALA and gray will contain PGB. During the ALA alone period, blue will contain ALA and gray will contain placebo. During the PGB alone period, blue will contain placebo and gray will contain PGB.

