### Dose Titration

Study medication will follow a flexible dose titration to MTD to balance tolerability and relief, with regular weekly calls by research personnel. This means that doses of study medication will not be further increased if intolerable AEs are encountered at higher doses or if “a lot” or “complete” pain relief is achieved. If AEs are experienced subsequent to a dose increase of study medications, the protocol will allow for dose reduction to the previous dosage level in order to improve tolerability. The MTD fixed dose week will be from days 25 to 31. However, if MTD is reached before day 25, that MTD dose will continue up to and including the day 25 to 31 period. For ALA, the maximum possible daily dose will be 1800 mg, and for PGB the maximum possible daily dose will be 450 mg. The MTD fixed dose week will be followed by a 7-day dose taper and 4-day complete washout. Daily pain ratings will be completed throughout the trial. During dose taper and washout periods only, patients may take acetaminophen, ≤8 tablets per day (325 mg per tablet) as needed. This rescue medication is very unlikely to affect the primary outcome measure of pain intensity during the MTD phase of each treatment period.

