### Trial Duration and Follow-Up Frequency

Each of the 3 treatment periods will be 6 weeks, for a total trial duration of 18 weeks. The nurse will phone patients weekly to evaluate AEs, guide drug titration, and encourage compliance. Patients will be seen in the clinic at the end of each treatment period for assessment of vital signs and measurement of secondary outcomes (Figure 4). Patients will be followed up by phone 2 weeks and 3 months after trial completion (including patients who were withdrawn from the trial prematurely) to document any subsequent AEs.

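### Adverse events are set to be compared at the MTD/end of period, after tolerability-guided dose adjustment, while other sections imply whole-period safety data; the comparison window needs reconciling

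*Protocol article*

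**What the plan says.** **Passages that place the AE comparison late in the period**

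- Protocol article, Abstract, Methods: "Secondary outcomes, assessed at MTD, will include global improvement, adverse events, mood, and quality of life".
- Trial Design describes "primary and secondary trial analyses comparing the 3 treatments using end-of-period outcomes".
- Dose Titration fixes the MTD week at days 25 to 31. Before that week, increases stop when intolerable AEs occur (or when pain relief is good enough), and after AEs "the protocol will allow for dose reduction to the previous dosage level in order to improve tolerability".

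**Passages that point to the whole period**

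- Trial Duration and Follow-Up Frequency: "The nurse will phone patients weekly to evaluate AEs, guide drug titration, and encourage compliance". Patients withdrawn early are also phoned after the trial about AEs.
- Outcome Measures and Safety Assessment lists AE frequency and severity, and any major AE, with no restriction to the MTD. It also makes the MTDs of both drugs secondary outcomes.
- Statistical Analyses puts everyone who took at least one dose into the safety analyses.

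**What the safety comparison is for**

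- Abstract, Objective: combinations with a nonsedating agent "would be as safe but more effective than either monotherapy without increasing overall AEs because of additive pain relief".
- Aims and Hypothesis: "The objective of this trial is to compare the safety and efficacy of a PGB+ALA combination to each monotherapy", followed by "Our primary hypothesis is that PGB+ALA has greater analgesic efficacy versus either monotherapy".

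**The concern.** The MTD is itself defined partly by AEs. A patient who cannot tolerate a step is held or moved back, separately within each treatment period, so by day 25 each treatment is being taken at a dose already chosen for tolerability. If one treatment is harder to tolerate, the adjustment absorbs part of that difference before the comparison is made. Patients who stopped before day 25 of a period contribute no MTD-week observation for it.

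The safety hypothesis concerns overall AEs, which is a statement about the whole exposure. A one-week comparison after dose adjustment answers a narrower question: how tolerable each treatment is at the dose the patient ended up on. That question is legitimate, but it is a different one.

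The protocol also supports two windows at once. If the choice between them is left until the data are seen, the safety conclusion could depend on it.

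**Working it through.** **1. Is there a plan figure to reproduce?** No. The protocol gives no AE rate by treatment, dose step or week, no safety margin and no precision target for AEs. The sample size (54 completers) was set for pain and enters below only as a number of pairs.

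**2. The passages side by side**

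| Section | What it fixes about AEs | Window |
|---|---|---|
| Abstract, Methods | AEs are among outcomes assessed at MTD | days 25-31 |
| Trial Design | basis of secondary comparisons | end of period |
| Trial Duration and Follow-Up Frequency | collection of AEs | weekly, throughout |
| Outcome Measures and Safety Assessment | AE frequency and severity; any major AE | not restricted |
| Statistical Analyses | safety population: all dosed | not stated |
| Statistical Analyses (secondary outcomes) | one last-week value for final-week questionnaires | does not cover AEs |

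Only the first two rows give a time for the treatment comparison, and both point to the end of the period. The others widen collection, outcome and population, but none names a different comparison window.

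**3. Direction of the effect: an illustration on assumptions.** Every input here is assumed, because the protocol has no AE data by dose step. Each simulated patient has a tolerance term (normal, SD 0.7). The AE burden is that term, plus drug effect × fraction of full dose, plus noise (SD 0.3 or 0.6). Burden above 1.2 is intolerable and causes a step back of one level and no further increase. There are four dose steps, and the two drugs' effects add on the combination. Full-dose effects for (PGB, ALA) were (1.0, 0.5), (1.0, 1.0), (1.5, 0.5) and (0.7, 0.3), giving eight settings with the two noise levels.

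| Contrast | Any intolerable AE during titration | Intolerable AE at the final MTD |
|---|---|---|
| Combination minus PGB | 11 to 42 points | about 0 to 6 points |
| Combination minus ALA | 24 to 63 points | 5 to 13 points |

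One setting in full (effects 1.0 and 0.5, noise 0.3):

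- During titration: 67.8% on the combination versus 43.9% on PGB, a difference of 67.8 − 43.9 = 23.9 points.
- At the MTD: 22.4% versus 17.7%, a difference of 4.7 points.

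Mean dose reached, as a share of the maximum, was 38-72% on the combination, 50-79% on PGB and 62-87% on ALA. Part of the lost difference therefore reappears as a lower MTD.

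Two cautions apply. The model builds in a less tolerable combination, so it shows what happens to a difference if one exists, not that one exists. The titration column also accumulates over four steps and the MTD column is one assessment, so some of the gap comes from counting over a longer time.

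**4. Precision, whichever window is used.** With 54 pairs and discordant proportion d (assumed), the 95% half-width at a small difference is 1.96 × √(d/54):

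- d = 20%: 1.96 × 0.0609 = 11.9 points
- d = 30%: 1.96 × 0.0745 = 14.6 points
- d = 40%: 1.96 × 0.0861 = 16.9 points
- d = 50%: 1.96 × 0.0962 = 18.9 points

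Power for a 10-point increase with d = 30% (20% versus 10% discordant): Φ((0.10 − 1.96 × 0.0745)/√((0.30 − 0.01)/54)) = Φ(−0.0461/0.0733) = Φ(−0.63), about 26%.

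These figures bear on how a null AE result should be read. They do not measure the effect of the window, because at the same d they apply equally to a whole-period comparison.

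**The case against.** The strongest reply is that a condensed abstract sentence is being set against a fuller body. The outcomes section does not tie AEs to the MTD, the safety set keeps every dosed patient, the last-week rule in Statistical Analyses is for questionnaires, and the assessment schedule (Figure 4) is not available here. The MTDs are outcomes in their own right, so a poorly tolerated treatment would show as a lower dose. An analysis plan that is not shown may settle the rest.

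Much of this stands, and it rules out several stronger readings that a reader might infer:

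- *That dose-limiting AEs are left out, or that patients who stop for AEs vanish.* The weekly calls, the unrestricted AE outcomes, the all-dosed safety set and the MTD outcome say otherwise. AEs can also persist at the MTD, so titration reduces intolerable ones rather than eliminating them.
- *That equal safety is formally tested and would be declared from a non-significant result.* The primary hypothesis concerns efficacy only. No safety margin, dedicated safety test or decision rule is stated.
- *That the cited PGB rates show the AE burden falls in titration.* The Introduction gives dizziness of 27%-46% and sedation of 15%-25% at 600 mg per day, with no timing. This trial's stated PGB maximum is 450 mg per day.

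The reply does not remove the inconsistency. Trial Design is body text and agrees with the Abstract. A population and a collection schedule do not define a comparison window. The dose reached is not the same information as the AEs experienced on the way to it. Nor is this a detail merely left to an analysis plan: a window is stated, and it fits the safety hypothesis poorly.

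**Conclusion.** The point holds as a matter of reconciliation and of choosing the better window. The stated timing places the AE comparison after tolerability-guided dose adjustment, whereas the collection, outcome and population statements suit a whole-period comparison. An analysis limited to days 25 to 31 would tend to understate AE differences and could not on its own support a claim about overall AEs.

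The direction follows from the titration rule. The size cannot be derived from the protocol, and the simulated figures depend on the assumed drug effects, additivity and step-back rule. Separately, at about 54 pairs and 20-50% assumed discordance, an AE difference would be known only to within roughly 12 to 19 points in either window, so absence of significance would be weak evidence of equal safety. The point should be addressed, but it does not affect the primary efficacy analysis.

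**What to change.** Reconcile the Abstract and Trial Design with the follow-up, outcome and safety-population text:

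- State that AE frequency and severity are compared between treatments over the whole dosing period (days 1 to 31, titration included), using the weekly call data in all dosed patients.
- Tabulate AE-related dose reductions and withdrawals by treatment, and report the MTD reached beside the AE results.
- Keep the MTD-week AE comparison as supportive, described as tolerability at the dose reached.
- Report differences with 95% confidence intervals, and say that a non-significant difference will not be read as showing equal safety.

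The cost is a wording change and a little more analysis. No new data, visits or changes to patient management are required. The downside is that reported AE rates will look higher and any safety statement will be limited to what the intervals support.
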